### Data collecting and monitoring

The scale of the study will be made into a form of online questionnaire, and participants will be guided how to fill in the questionnaire before after signing the informed consent. Data researchers can receive the results of the scale and blood test through the internet without communication with participants, and record the data on the case report forms (CRFs) to ensure the integrity of the RCT and protect the privacy of the participants. Data will be safekept by the data researchers of our team and monitored by the Ethics Committee of Dongzhimen Hospital, Beijing University of Traditional Chinese Medicine every 3 months.

### Statistical analysis

Data of this clinical trial will be analyzed using SPSS version 23.0 software (released 2015, IBM Corp., Armonk, NY, USA). All data will be presented as mean ± standard deviation or value and its percentage. Demographic (age, sex, course, family history, the dosage of drugs) will be compared between two groups as the baseline assessment. The data of the observation indicators are all measurement data. According to the normal test, select the appropriate parameter test or non-parameter test. A paired *t* test or Wilcoxon signed-rank test can be used for comparison before and after treatment within group. Independent sample *t* test or Wilcoxon rank-sum test can be used for comparison between groups. In two groups, all the statistical tests will be performed with bilateral tests, and *P*< 0.05 indicates the difference deemed statistically significant.

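### The Statistical analysis section fixes unadjusted t or rank-sum tests chosen by a normality test, and adds within-arm P values without naming the between-arm contrast as the inference; one baseline-adjusted week-16 model would use the same data better

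*Protocol article*

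**What the plan says.** In the protocol article, Statistical analysis, the choice of method is left to the data: "According to the normal test, select the appropriate parameter test or non-parameter test". Between arms, an independent-sample t "test or Wilcoxon rank-sum test can be used for comparison between groups". Within each arm, a paired t "test or Wilcoxon signed-rank test can be used for comparison before and after treatment within group". Both kinds of test share one rule: "all the statistical tests will be performed with bilateral tests", and P below "0.05 indicates the difference deemed statistically significant". On summaries: "All data will be presented as mean ± standard deviation or value and its percentage".

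The section names no covariate and no transformation. It does not say whether the between-arm test is applied to the change or to the follow-up value, or which of the two kinds of test carries the conclusion. Primary outcomes defines the endpoint as change in the concentrations of TPOAb, TgAb and thyroid hormones including TSH, measured at baseline and weeks 8, 16, 24 and 32. The questionnaires also have a baseline value. Under Study design, controls are only observed until week 16 and then receive the same acupuncture.

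**The concern.** The section makes positive choices, and better use of the same data is available.

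- **Baseline.** With about 24 evaluable patients per arm, leaving baseline out of the model gives away precision.
- **Estimand.** The t test contrasts means and the rank-sum test contrasts ranks. Letting a normality test decide means the data choose which question is answered. Sample size estimation justifies 60 patients by the wish for a sound mean and effect size.
- **Scale.** If antibody values are right-skewed, a mean ± SD is dominated by a few high values, and a ratio is the more natural effect measure.
- **Within-arm tests.** A significant fall under acupuncture beside a non-significant one under observation can be taken for efficacy, although no comparison between arms has been made. After week 16 there is no untreated comparator at all.

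**Working it through.** **Sample size.** 30 per arm with 20% dropout leaves 30 × (1 − 0.20) = 24 per arm, inside the 20–30 rule the article cites. The article states no power, SD or effect size, so there is no power figure to reproduce.

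**Variance ratios.** Take equal variances at baseline and follow-up, with correlation r. In units of the follow-up variance, the follow-up analysis has variance 1, the change score 2(1 − r), and ANCOVA 1 − r².
- ANCOVA against change: (1 − r²)/[2(1 − r)] = (1 + r)/2. This is 0.80 at r = 0.6, 0.90 at 0.8 and 0.95 at 0.9.
- ANCOVA against follow-up value: 1 − r². This is 0.64, 0.36 and 0.19.

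These ratios need no skew assumption, so they apply to questionnaire scores as well.

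**Power for an antibody.** Assumptions, none of them in the article: log-normal marker, true 30% fall (log effect ln 0.7 = −0.357), log-SD s of 0.8 or 1.2, r of 0.6, 0.8 or 0.9, 24 per arm, two-sided 0.05.
- Columns 1 and 2 are simulated on raw change (4,000 runs per row, standard error at most √(0.25/4000) = 0.8 points, Shapiro–Wilk gate).
- Columns 3 and 4 are noncentral-t power with standardised effect 0.357/[s√(2(1 − r))] for log change and 0.357/[s√(1 − r²)] for log ANCOVA.

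| s, r | Plan's gated rule | Always rank-sum | t on log change | Log ANCOVA |
|---|---|---|---|---|
| 0.8, 0.6 | 29% | 29% | 39% | 47% |
| 0.8, 0.8 | 48% | 49% | 67% | 71% |
| 0.8, 0.9 | 77% | 77% | 92% | 93% |
| 1.2, 0.6 | 15% | 15% | 20% | 24% |
| 1.2, 0.8 | 25% | 25% | 36% | 39% |
| 1.2, 0.9 | 44% | 44% | 62% | 64% |

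Separate simulations of the same settings agree to within a few points.
- Log ANCOVA gains about 10 to 23 points over the plan's rule, mostly between columns 1 and 3, which is the log scale.
- Baseline adjustment, column 4 less column 3, adds about 1 to 8 points (0.5 to 7 in repeat simulations), most at r = 0.6.
- Columns 1 and 2 agree, so the gate costs no power against always using the rank test.
- If follow-up values are tested instead, which the section permits, simulated power of the gated rule is only about 30–31% at log-SD 0.8 and 15–16% at 1.2, whatever r is.

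**Type I error.** With no effect (24 per arm, log-SD 0.5 and 1.0, r 0.5 to 0.9), the gated between-arm test rejected in 3.9% to 6.0% of simulated trials, which is near nominal.

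**Within-arm contrast.** With no treatment effect and independent arms, let each arm's test reject with probability p. Significance in the acupuncture arm only has probability p(1 − p).
- No common trend: 0.05 × 0.95 = 0.0475, about 5%.
- Worst case, p = 0.5: 0.5 × 0.5 = 25%.
- Simulation with a drift of 0.3 SD common to both arms: 16–23%.

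**The case against.** Several stronger readings are tempting and should not be drawn.

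- **That the plan ignores baseline.** The primary outcome is a change, so baseline can enter by subtraction. What stands is that it is not a covariate and that the tested quantity is unstated.
- **That the plan ignores skew.** The rank-test branch is its answer to non-normality. Skew is itself assumed, and for TSH the assumption is weaker because entry requires thyroid hormone in the normal range. What stands is the lack of a log-scale estimate and the blanket mean ± SD.
- **That the normality gate causes false positives or lost power.** Neither was found. The point is prespecification.
- **That falls must occur through regression to the mean.** Diagnosis requires an elevated antibody, but the article sets no numeric threshold and does not say that the qualifying value is the baseline value.
- **That a rank test leaves nothing for planning the next trial.** Means and SDs are to be reported whichever test is used.
- **That efficacy will be judged within arms.** The article does not say so; it also plans between-arm tests.

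The power gain is also partly built in, because the data were generated from the model that log ANCOVA assumes. The table therefore says nothing about questionnaire scores.

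Finally, this is a pilot reported in a condensed article, it claims no power, and it concedes that its results may be imprecise. Covariates and transformations are often left to a fuller document. That would answer a complaint about missing detail, but the section names its tests and its selection rule, and those choices can be improved.

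**Conclusion.** The point holds as a free improvement, not as an error that invalidates the trial. The size rests on assumptions about distribution, SD, correlation and effect that the article does not supply. Within the ranges used, power is about 15–77% for the plan's rule on change and 24–93% for log-scale ANCOVA, with the log scale responsible for most of the difference. What does not depend on skew is the variance ratio of (1 + r)/2 or 1 − r², the data-driven switch between a mean and a rank contrast, and the absence of a statement that the between-arm comparison is the inference. The risk of a misleading within-arm pattern runs from about 5% with no trend to 25% at worst, and it matters only if that pattern is read as evidence of efficacy.

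**What to change.** Amend Statistical analysis as follows.

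1. Name the between-arm contrast at week 16, the last assessment before controls start acupuncture, as the inference.
2. Analyse it by ANCOVA with arm and the baseline value, on the log scale for antibodies and TSH and on the original scale for questionnaire scores.
3. Report the geometric-mean ratio or adjusted mean difference with its 95% confidence interval.
4. Drop the normality gate and keep the rank-sum test as a sensitivity analysis.
5. Summarise antibodies by geometric mean or median with interquartile range.
6. Present within-arm changes descriptively, without P values.

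The cost is a few lines of text. No extra data or patients are needed, and SPSS 23, the software already named, can fit the model.

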#### Withdrawal criteria

Participants will be withdrawn from the study if the following occurs:
Less than 75% of total treatment (i.e., participating in fewer than 36 of the 48 scheduled treatment sessions)Participant’s decision to withdraw from the study at any time for any reason; andOccurrence of any unexpected serious side effects.

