### Blinding

Because of the particularity of acupuncture, it is difficult to blind clinical researchers and participants. In this study, only two data researchers in charge of the collection, preservation, and analysis of data are blinded. Participants will provide information to the date researchers through online questionnaires without communication between both sides. So that data researchers cannot be aware of the grouping allocation. In this study, the data of each participant will be collected every 8 weeks, hence the researchers also cannot infer the grouping allocation through data information. Data researchers will be asked to speculate the grouping allocation to evaluate the implementation of the blind method.

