### Sample size estimation

This study aims to evaluate the clinical effectiveness and safety of PNHM for HT. The estimation of sample size should be based on the feasibility, precision about the mean, and variance [24]. It is stipulated that the sample size of exploratory trials is 20–30 per group in China [25]. With consideration of the drop rate of 20% and the feasibility of the study, we finally plan to recruit 60 participants in total to assure the validity of the mean and effect size.

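### The between-group tests named take one value per patient, so unless the SAP adds a rule, week-8 data of patients who leave go unused at week 16, and loss that differs by arm can bias that comparison in either direction

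*Protocol article*

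**What the plan says.** The Statistical analysis section of the protocol article names two families of test. Within a group: a paired t test, or "Wilcoxon signed-rank test can be used for comparison before and after treatment within group". Between groups: an independent-sample t test, or "Wilcoxon rank-sum test can be used for comparison between groups". It names no model that takes several visits together, and it does not mention missing values or an analysis set.

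Other sections set the conditions under which those tests will run:

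- Primary outcomes: antibodies and hormones are measured at baseline and weeks 8, 16, 24 and 32.
- Study design: allocation is 1:1, and controls are observed until week 16 and then receive acupuncture. Week 8 is therefore the only other post-baseline visit at which treated patients are compared with untreated controls.
- Sample size estimation: "With consideration of the drop rate of 20% and the feasibility of the study, we finally plan to recruit 60 participants in total".
- Withdrawal criteria: one ground for leaving is the participant's "decision to withdraw from the study at any time for any reason".
- Blinding: "it is difficult to blind clinical researchers and participants".
- Intervention: 48 sessions, three a week for 16 weeks. Until week 16 only the experimental group attends them.

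**The concern.** A two-sample t test or rank-sum test at week 16 needs one week-16 value from each patient. Without imputation, someone seen at week 8 who leaves before week 16 drops out of the comparison, and the week-8 value already collected is not used.

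That is harmless if leaving has nothing to do with outcome, or if it relates to outcome in the same way in both arms. Neither is easy to assume here. Patients know their group. One arm carries the burden of frequent needling; the other waits untreated with acupuncture promised later. If outcome-related leaving differs between arms, those left at week 16 are no longer comparable, and the effect estimate this pilot is meant to supply is shifted.

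The point concerns ordinary drop-out. The attendance-based withdrawal rule in the same section is a separate matter.

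**Working it through.** **The plan's own figure.** The total of 60 rests on a convention ("the sample size of exploratory trials is 20–30 per group in China") and a drop-out allowance. No effect size, SD or power is given, so it cannot be reproduced from a power formula. It is coherent: 60 × 0.20 = 12 lost, 30 × (1 − 0.20) = 24 left per arm, 24 / 0.80 = 30, and 24 lies within 20–30.

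**Formula.** Let the week-8 and week-16 changes each have SD 1 and correlation ρ, with no true effect, and let leaving after week 8 depend only on the week-8 change. The mean week-16 change of those who stay is then ρ × m, where m is the mean week-8 change of those who stay. The bias of the week-16 difference is

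ρ × (m in acupuncture − m in control).

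The difference between arms decides both its size and its sign.

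**Extreme selection.** If exactly the worst 20% at week 8 leave one arm and leaving in the other is random, m = φ(0.842) / 0.80 = 0.280 / 0.80 = 0.35 in that arm and 0 in the other. For ρ = 0.3, 0.5 and 0.7 the bias is 0.105, 0.175 and 0.245 SD. Simulation with 30 per arm and 6 lost gives about 0.10, 0.17 and 0.23 SD. False significance favouring acupuncture rises from 2.5% to about 5–6%, 9% and 14%.

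**Graded selection.** Here the odds of leaving rise by a stated ratio per SD of worse week-8 change (30 per arm, 6,000 simulated trials per scenario). The ratios, correlations and timing are assumptions; the article gives none of them.

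| Assumed mechanism | Bias at week 16, available cases |
|---|---|
| 20% lost per arm; odds ratio 2 in acupuncture, random in control; ρ = 0.6; half of the loss after week 8 | 0.04 SD towards acupuncture |
| 20% lost per arm; odds ratio 4 in acupuncture, random in control; ρ = 0.8; all after week 8 | 0.17 SD towards acupuncture |
| 20% lost per arm; odds ratio 4 in acupuncture, 2 in control | 0.07 SD towards acupuncture |
| 20% lost per arm; same mechanism in both arms | about 0 |
| 20% lost per arm; outcome-related in control only | up to 0.18 SD against acupuncture |
| 10% lost by week 16; otherwise as the first two rows | 0.02 to 0.09 SD towards acupuncture |

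When only the acupuncture arm loses non-responders, the two-sided rejection rate runs from the nominal 5% to about 9% at 20% loss.

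**Scale.** With 24 per arm the standard error of the difference is √(2/24) = 0.289 SD. The range 0.04 to 0.17 SD is therefore 0.04 / 0.289 = 0.14 to 0.17 / 0.289 = 0.59 of a standard error.

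**Using week 8.** A likelihood estimate that keeps the week-8 values of those who leave has bias within 0.01 SD in every scenario, whichever arm loses patients. Its standard error is about 1–7% smaller.

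**The case against.** A reader might infer that the plan deletes patients with missing values. It does not say so. The Statistical analysis section is silent on missing data, says only that the tests may be used, and a t test can follow imputation. A condensed article may leave such a rule to the full protocol or SAP, so the silence itself is no finding. What stands is that the methods it does name cannot by themselves use an earlier visit.

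A reader might also infer that the bias favours acupuncture. That needs non-responders to leave mainly from the acupuncture arm. Controls are unblinded too and wait 16 weeks untreated, so they may also leave on outcome. The documents do not settle which arm, if either, will do so.

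The 20% is a recruitment allowance with no split by arm, reason or time, in a study of 33 weeks. Placing all of it before week 16 is an upper reading, which is why the 10% row is shown.

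The link to the primary outcomes is indirect. Patients cannot feel antibody levels, and the Data collecting and monitoring section sends blood results to data researchers who have no contact with participants. If leaving follows symptoms correlated 0.3 with antibody change (an assumption), the bias falls to about 0.015–0.06 SD and rejection to 5.2–6.0%. The link is more direct for the self-reported scales.

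Finally, the effect is well under one standard error in a pilot whose Discussion already concedes limited accuracy. That limits the urgency. It does not make the single-visit test the better choice, since the data needed are collected anyway.

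**Conclusion.** The concern holds in a conditional form. The named between-group tests take one value per patient, so unless the SAP adds a rule, the week-8 data of patients who leave are lost to the week-16 comparison. Outcome-related loss that differs between arms can then bias that result in either direction: about 0.04–0.17 SD towards acupuncture if non-responders leave that arm only, about zero if the arms behave alike, similar in size against acupuncture if it happens only in controls, and roughly half as large at 10% loss by week 16.

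These sizes rest on assumed correlations, drop-out mechanisms and timing; only the 20% allowance, the 1:1 allocation and the visits come from the article. The case for change does not depend on the direction, because a model that uses week 8 removes the part of the bias that week 8 explains in either arm. The change should be made, but the point does not invalidate the trial.

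**What to change.** Make the main between-group analysis a mixed model for repeated measures:

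- outcomes at weeks 8 and 16 fitted together;
- fixed effects for group, visit and group-by-visit;
- unstructured covariance (three parameters for two visits, feasible at 24–30 per arm);
- all randomised patients with any post-baseline value;
- log scale for the antibodies;
- the week-16 group contrast as the result.

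Keep the t test or rank-sum test on available week-16 values as a sensitivity analysis.

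The cost is analysis wording. No new data are needed, and the SPSS package already named has a mixed-model procedure. The downside is reliance on missingness being random given week 8, which is still weaker than what the available-case test assumes, and on a normal model on the log scale. Patients who leave before week 8 add nothing to either analysis, and the precision gain is only a few percent.

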### Quality control

This clinical trial has been reviewed by experts of general surgery, acupuncture, methodology, etc. Before the start of this trial, all acupuncturists were required to participate in training of standard operation procedure (SOP) to ensure every acupuncturist is familiar with the trial scheme and process. During the time this trial is carried out, the research team will conduct workshops every 2 months to summarize the experience and evaluate the progress of the trial, clinical feasibility, and side effects. The supervisor shall regularly check the progress of the trial.

## Discussion

The current treatment of HT focuses mainly on the symptom of hypothyroidism that occurs in the later stage of the disease via orally-taken LT4 in a long-term. However, there are not yet any effective treatments for symptoms of neck pressure, fatigue, mood swings, infertility, and others. Comprehensive management methods adopted to delay the progression of the disease or reduce the degree of hypothyroidism deserve further exploration.

Acupuncture has advantages in alleviating clinical symptoms, such as neck pressure, fatigue, and mood swings, and hardly has side effects. Some studies also suggest that acupuncture can stimulate the body to produce a series of neurohumoral immune responses and as a result improve immune disorder state [32]. This suggests that acupuncture has potential therapeutic value for HT. The abovementioned acupuncture treatments can be referred to ancient acupoints for treating thyroid diseases and the experience of modern acupuncture experts. In our earlier clinical observations, this acupuncture method can improve clinical symptoms of HT patients, and some patients’ thyroid-related antibody concentrations have decreased.

Some studies suggest a positive correlation between antibody concentration and the extent of thyroid inflammatory cell infiltration [33, 34]. Thyroid antibody concentrations are also positively correlated with the quality of life of HT patients. Thus, we have chosen antibody concentration as one of the main efficacy indicators to objectively reflect the subject’s immune status. Meanwhile, we will also observe whether the TSH is further stabilized or decreased to the normal range, so as to potentially reduce the dose of FT4 with the help of acupuncture. The use of multiple symptom score scales as secondary efficacy indicators is to fully evaluate the effect of acupuncture treatment on clinical symptoms of HT patients.

The mechanism of acupuncture treatment is complicated and is completely different from the specific target of “one key to one lock” in western pharmacology. On the one hand, there is no ideal placebo-controlled method for clinical research of acupuncture [35]. On the other hand, the non-specific clinical effects caused by placebo cannot be regarded as an insignificant or unimportant part [36]. Research methods that try to strip the biological and psychological effects of acupuncture may contradict the development model of modern medical bio-psycho-social medicine. Therefore, the non-specific effects of acupuncture also require attention. In order to reflect the comprehensive effect of acupuncture treatment, we have chosen a blank control to try to observe the effect of acupuncture treatment in the presence of a placebo effect.

There are two limitations in this study. First, the sample size is small, and the main research purpose of this study is to evaluate the feasibility and clinical value of the treatment of HT by PNHM, so the research results may not accurately reflect the true clinical effect of acupuncture on HT. Second, considering the acceptance of the subject, a blank control is assigned as the control group in this study, which could not exclude the non-specific therapeutic effect or placebo effect of acupuncture. At the same time, we cannot prove the specific therapeutic effect of the selected acupoints and acupuncture methods.

